## 474 6.5 Efficacy Assessments

475 Screening assessments must include magnetic resonance imaging (MRI) with gadoxetate  
476 disodium as well as dual-tracer PET-CT with contrast enhanced triphasic CT scan of the liver  
477 for tumor contouring and treatment planning for SBRT.

478 Follow-up imaging with MRI with gadoxetate disodium injection and dual-tracer PET-CT  
479 scan with contrast-enhanced triphasic CT scans every 3 months after SBRT will be arranged  
480 for treatment response evaluation by RECIST 1.1, mRECIST, and PERCIST  
481 (APPENDIX 4 and APPENDIX 5) and surveillance for recurrence/relapse.

482 At the investigator's discretion, scans should be repeated at any time if progressive disease is  
483 suspected.

484 Confirmation of progression guidelines are set for the following reasons:

- 485 • for patient management and treatment decisions
- 486 • when scans are evaluated by two independent radiologists.

Confirmed objective disease progression refers to either of the following scenarios: 1. clinical progression/deterioration followed by a radiologic verification scan (progressive disease [PD] by RECIST 1.1, mRECIST, and PERCIST); or 2. in the absence of significant clinical deterioration, radiologic PD by RECIST 1.1, mRECIST, and PERCIST followed by a second radiologic confirmation scan with PD assessed according to the specific confirmation of progression criteria listed below. The confirmatory scan should occur preferably at the next scheduled imaging visit and no earlier than 4 weeks following the date of the immediate prior assessment of PD.

Immediate prior radiologic progression would be considered confirmed if any the following criteria are met in the confirmatory scan:

- $\geq 20\%$  increase in the sum diameters of target lesions (TLs) compared with the nadir at 2 consecutive visits, with an absolute increase of at least 5 mm in sum of diameters compared to nadir,

- and/or significant progression (worsening) of non-target lesions (NTLs) and/or of pre-existing new lesions at the confirmatory scan time-point compared with the immediate prior time-point (Note: Pre-existing new lesions are evaluated as NTLs at the confirmatory scan time-point),

- and/or additional new unequivocal lesions at the confirmatory scan time-point.

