If progression is not confirmed, in the absence of significant clinical deterioration, then the patient should continue the study and on-treatment assessments until the next PD which will also require a follow-up confirmation scan. If the first PD is not confirmed by the immediate next scan, then the Investigator should not change the PD assessment of the first scan.

If a patient discontinues treatment (and/or receives a subsequent anticancer therapy) prior to radiologic progression, then the patient should still continue to be followed until confirmed objective disease progression.

Following confirmed progression, patients should continue to be followed up for survival every 2-3 months until death or until patient refusal.

Please refer to APPENDIX 4 and APPENDIX 5 for the definitions of objective response by RECIST 1.1, mRECIST, and PERCIST. The method of determination of metabolic tumor volume (MTV) and total lesion glycolysis (TLG) and total lesion activity (TLA) based on PET-CT scan with FDG and ACC respectively for subsequent exploratory statistical analyses were described in APPENDIX 5.

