#### APPENDIX 4. RECIST 1.1 and mRECIST

| RECIST 1.1                                                                                                                                                                               | mRECIST                                                                                                                                                                                                                        |
|------------------------------------------------------------------------------------------------------------------------------------------------------------------------------------------|--------------------------------------------------------------------------------------------------------------------------------------------------------------------------------------------------------------------------------|
| CR – Disappearance of all target lesions                                                                                                                                                 | CR – Disappearance of any intratumoral arterial enhancement in all target lesions                                                                                                                                              |
| PR – At least a 30% decrease in the sum of diameters of target lesions, taking as reference the baseline sum of the diameters of target lesions                                          | PR – At least a 30% decrease in the sum of diameters of viable (enhancement in the arterial phase) target lesions, taking as reference the baseline sum of the diameters of target lesions                                     |
| SD – Any cases that do not qualify for either partial response or progressive disease                                                                                                    | SD – Any cases that do not qualify for either partial response or progressive disease                                                                                                                                          |

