| PD – An increase of at least 20% in the sum of the diameters of target lesions, taking as reference the smallest sum of the diameters of target lesions recorded since treatment started | PD – An increase of at least 20% in the sum of the diameters of viable (enhancing) target lesions, taking as reference the smallest sum of the diameters of viable (enhancing) target lesions recorded since treatment started |

CR, complete response; PD, progressive disease; PR, partial response; SD, stable disease.

1097

1098

1099 **APPENDIX 5. PERCIST 1.0**

|                         | PERCIST 1.0                                                                                                                                                                                                                                                                                                                                                                                                                                                                                                                                                                                                                        |
|-------------------------|------------------------------------------------------------------------------------------------------------------------------------------------------------------------------------------------------------------------------------------------------------------------------------------------------------------------------------------------------------------------------------------------------------------------------------------------------------------------------------------------------------------------------------------------------------------------------------------------------------------------------------|
|                         | 
1. Measurable target lesion in hottest single tumor lesion SUL of “maximal 1.2 cm diameter volume ROI in tumor” (SUL peak). SUL peak is at least 1.5 fold greater than liver SUL mean + 2 SDs (in 3cm spherical ROI in normal right lobe of liver). If liver is abnormal, primary tumor should have uptake <math>> 2.0 \times</math> SUL mean of blood pool in 1cm diameter ROI in descending thoracic aorta extended over 2cm z-axis..
 
2. Tumor with maximal SUL peak is assessed after treatment. Although typically this is in same region of tumor as that with highest SUL peak at baseline, it need not be.
 |

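### Appendix 4 defines RECIST 1.1 and mRECIST response and progression on target lesions only, in conflict with Section 6.5 and Appendix 5, so it is undetermined whether a new lesion is a PFS event or bars a response

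*Protocol*

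**What the plan says.** PFS and best objective response are the co-primary endpoints, each assessed by RECIST 1.1, mRECIST and PERCIST (synopsis, Sections 2.1 and 8.1.1).

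- **Appendix 4.** RECIST 1.1 progression is "An increase of at least 20% in the sum of the diameters of target lesions", measured from the smallest sum since treatment started. The mRECIST entry is "An increase of at least 20% in the sum of the diameters of viable (enhancing) target lesions", on the same principle. Complete response under RECIST 1.1 is "Disappearance of all target lesions". Partial response is likewise a change in the target-lesion sum, and stable disease is the remainder.
- **Section 6.5.** It sends the reader to the appendices: "Please refer to APPENDIX 4 and APPENDIX 5 for the definitions of objective response by" the three criteria. Its own list for confirming a progression already called adds an absolute floor, "with an absolute increase of at least 5 mm in sum of diameters compared to nadir". It also admits worsening of non-target lesions or of new lesions seen earlier ("Pre-existing new lesions are evaluated as NTLs at the confirmatory scan time-point"), and "and/or additional new unequivocal lesions at the confirmatory scan time-point".
- **Appendix 5.** Under PERCIST, new acetate- and/or FDG-avid lesions typical of cancer are progressive metabolic disease. A partial metabolic response requires that there be no new lesions.
- **Combining the criteria.** Sections 2.1, 6.5 and 8.1.1 join the three with *and*. The synopsis gives an unjoined list in its PFS definition.

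**The concern.** SBRT is directed at the lesions contoured at baseline. A definition that looks only at those lesions measures what happens inside the treated volume and is silent about new HCC outside it. For a bridging study, new HCC elsewhere in the liver is plainly relevant to whether the patient still meets the transplant criteria.

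The protocol gives three different accounts of progression: Appendix 4 ignores new lesions, Section 6.5 uses them to confirm, and Appendix 5 makes them progression outright. Two assessors following different pages could classify the same scan differently on both co-primary endpoints. If Appendix 4 were followed as written, the RECIST 1.1 and mRECIST readings could only err in the favourable direction for patients with new lesions. For small target sums the conflict runs the other way, because Appendix 4 calls progression at growth that falls short of the size criterion in Section 6.5.

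**Working it through.** **Sample size.** The protocol's 28 patients (60% versus 85%, two-sided 0.05, 80% power) is close to what standard one-sample formulas give: 26 by normal approximation and 30 with continuity correction. Allowing for 20% dropout, 28 / 0.80 = 35, as stated. None of these inputs is touched by this point.

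**1. One patient followed through the definitions.** Take target lesions down by at least 30% (total and viable sums), one new HCC lesion outside the treated volume, no death, and assume any progression called is later confirmed.

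- RECIST 1.1 and mRECIST under Appendix 4: partial response, since only the target sum is examined.
- PERCIST under Appendix 5: progressive metabolic disease if the new lesion is avid for either tracer; not progressive on that limb if it is avid for neither.
- RECIST 1.1 and mRECIST if new lesions count at the first call, as Section 6.5 implies: progression.

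Whether this is a PFS event:

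| RECIST 1.1 / mRECIST read by | New lesion | All three criteria needed | Any one suffices |
|---|---|---|---|
| Appendix 4 as written | avid | no event | event |
| Appendix 4 as written | not avid | no event | no event |
| New lesions counted, as Section 6.5 implies | avid | event | event |
| New lesions counted, as Section 6.5 implies | not avid | no event | event |

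The literal *and* of Sections 2.1, 6.5 and 8.1.1 gives the first outcome column. The second is one possible reading of the synopsis list. Four of the eight cells are events, so the same patient is progression-free or not according to the page followed.

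**2. Best response.** The same patient is a responder on RECIST 1.1 and mRECIST under Appendix 4. The new lesion bars a partial metabolic response under Appendix 5. No rule says which of the three is the response for the endpoint.

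**3. The size rules.** Appendix 4 calls progression at an increase of 0.20 × nadir. The size limb in Section 6.5 needs the larger of 0.20 × nadir and 5 mm. They coincide when 0.20 × nadir = 5 mm, that is, at a nadir of 5 / 0.20 = 25 mm.

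| Nadir sum (mm) | Appendix 4 (mm) | Section 6.5 size limb (mm) |
|---|---|---|
| 10 | 2 | 5 |
| 15 | 3 | 5 |
| 20 | 4 | 5 |
| 25 | 5 | 5 |
| 30 | 6 | 6 |

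Below 25 mm the rules disagree; at 25 mm and above they agree. Such nadirs are within reach: a 30% reduction from a baseline sum of 35 mm gives 0.70 × 35 = 24.5 mm, and eligibility (Section 3.1) caps total tumour diameter at 8 cm, with no lower limit in that criterion.

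**The case against.** A reader might infer that HCC outside the treated volume is not progression in either co-primary endpoint. The documents do not support that. PERCIST is a named component of both endpoints and captures avid new lesions. Section 6.5 speaks of new lesions already present at the earlier scan and of additional ones, which presupposes that a new lesion can form part of the first progression call. PFS also requires confirmed progression, so Section 6.5 bears on the endpoint directly. The PFS event is lost only on particular combinations: the literal *and* with Appendix 4 governing, or a lesion that is not avid.

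Four further points on that side:

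- RECIST 1.1 and mRECIST are adopted by citation, and Appendix 4 may be only a summary. That is possible, but the protocol does not say so, and Section 6.5 names the appendix as a place to find the definitions.
- A stricter confirmation threshold can be a deliberate two-step design, and Section 6.5 says what happens when progression is not confirmed. This stands in part: a growth below 5 mm can still be confirmed later or through another limb, so the conflict concerns the size criterion only. No passage presents the difference as intended.
- A lesion that appears after a documented response need not cancel that response. This stands, and limits the response problem to new lesions present at the time point being scored.
- PERCIST might be thought to make good the omission. It does so only in part, because its partial response itself refers back to absence of progression by RECIST.

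**Conclusion.** The point holds as a contradiction within the protocol. Appendix 4 omits new lesions, non-target progression and the absolute floor for both RECIST 1.1 and mRECIST, against Section 6.5 and Appendix 5. A patient with shrinking targets and new HCC can therefore be scored as not progressing, and as a responder, on two of three criteria; the PFS consequence depends on tracer avidity and on an unsettled combination rule.

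The only size that follows from the documents is the 25 mm nadir boundary. A reader might go on to put a figure on inflated PFS or on a raised chance of a false positive response result. That would need rates of target progression, of new lesions and of discordant responders, together with a critical number of responders, and the protocol states none of these. It also does not say how new lesions were treated in the 60% benchmark. The direction of the possible error on the RECIST 1.1 and mRECIST readings is clear; its magnitude is not derivable. The point should be settled before response and PFS are analysed.

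**What to change.** Reconcile Appendix 4 with Section 6.5 and Appendix 5:

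1. State overall response in Appendix 4, so that unequivocal new lesions and non-target progression count as progression and preclude complete or partial response at that time point.
2. Use one consistent size threshold for the first progression call and for its confirmation. Which threshold is for the sponsor to decide, since confirmed progression also stops study treatment under Section 5.2.
3. State how RECIST 1.1, mRECIST and PERCIST combine into a single PFS event with a single date, and into a single best response. Use the same wording in the synopsis and Sections 2.1, 6.5 and 8.1.1. Without this, item 1 alone leaves the status of a new lesion open.

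The cost is a wording amendment and its IRB submission. No scans are added, because the planned PET is whole-body and the contrast CT covers the whole abdomen (Appendix 3), and the sample size is unchanged. The downside is that reported PFS and response may be less favourable.

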| Primary Objectives | 
 
• Progression-free survival (PFS), calculated from start of SBRT to the date of radiologically confirmed progressive disease based on RECIST 1.1, mRECIST, PERCIST or death from any cause
 
• Best objective response as defined per RECIST, mRECIST, and PERCIST
 
                                                                                                                                                                                                                                                                                                                                                                                                                                                                                                                                                                                                                                                                                                                                                                                                                                                                                                                        |

|                               |                                                                                                                                                                                                                                                                                                                                                                                                                                                                                                                                                                                                                                                                                                                                                                                                                                                                                                                                                                                                                                                                                                                                                                                                                                                                       |

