| Objective response | CMR – complete resolution of FDG and ACC uptake within measurable target lesion so that it is less than mean liver activity and indistinguishable from surrounding background blood-pool levels. Disappearance of all other lesions to background blood pool levels. Percentage decline in SUL should be recorded from measurable region, as well as (ideally) time in weeks after treatment was begun (i.e., CMR-90, 4). No new FDG-avid lesions in pattern typical of cancer. If progression by RECIST, must verify with follow-up.                                                                                                                                                                                                                                                      |
|                    | PMR – reduction of minimum of 30% in target measurable tumor ACC and/or FDG SUL peak. Absolute drop in SUL must be at least 0.8 SUL units, as well. Measurement is commonly in same lesion as baseline but can be another lesion if that lesion was previously present and is the most active lesion after treatment. ROI does not have to be in precisely same area as baseline scan, though typically it is. No increase, > 30% in SUL or size of target or nontarget lesions (i.e., no PD by RECIST or IWC) (if PD anatomically, must verify with follow-up). Reduction in extent of tumor ACC and FDG uptake is not requirement for PMR. Percentage decline in SUL should be recorded, as well as (ideally) time in weeks after treatment was begun (i.e., PMR-40, 3). No new lesions. |
|                    | SMD – not CMR, PMR, or PMD. SUL peak in metabolic target lesion should be recorded, as well as (ideally) time from start of most recent therapy, in weeks (i.e., SMD -15, 7).                                                                                                                                                                                                                                                                                                                                                                                                                                                                                                                                                                                                              |

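### The PERCIST partial-response row in Appendix 5 allows size growth up to 30% and equates that with no RECIST progression, but Appendix 4 sets RECIST progression at 20%

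*Protocol*

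**What the plan says.** The Synopsis (Study Design) makes progression-free survival and objective response co-primary. Sections 2.1 and 8.1.1 define best objective response by RECIST 1.1, mRECIST and PERCIST.

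- **Appendix 5, PMR row.** The metabolic requirement is "reduction of minimum of 30% in target measurable tumor ACC and/or FDG SUL peak", with an absolute fall of at least 0.8 SUL units. The growth condition is "No increase, > 30% in SUL or size of target or nontarget lesions (i.e., no PD by RECIST or IWC", where the parenthesis closes. The row continues: "if PD anatomically, must verify with follow-up".
- **Appendix 4.** RECIST 1.1 progression is "An increase of at least 20% in the sum of the diameters of target lesions", and mRECIST progression is "An increase of at least 20% in the sum of the diameters of viable (enhancing) target lesions". Both are counted from the smallest sum since treatment started.
- **Section 6.5.** A confirmatory scan needs the same 20% over nadir, "with an absolute increase of at least 5 mm in sum of diameters compared to nadir". It is to be taken "no earlier than 4 weeks following the date of the immediate prior assessment of PD".
- **Appendix 5, closing notes.** A 20% linear increase is equated with a 73% volume increase, to justify the 75% limit for growth in total lesion glycolysis or activity (TLG/TLA).

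**The concern.** The words in parentheses present the 30% limit as another way of saying that there is no RECIST progression. Nowhere in the protocol does RECIST progression begin at 30% of size. It begins at 20%, and the closing notes of Appendix 5 use the same 20% benchmark. For growth between the two figures, the row therefore gives two answers: PMR by the number, not PMR by its explanation. It does not say which governs.

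PMR counts towards a co-primary response endpoint. If the number is followed inside the band, patients whose tumours have reached the RECIST growth threshold are counted as responders. If the explanation is followed, they are not.

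**Working it through.** **1. The plan's own figure.** Volume change for linear growth g is (1 + g)³ − 1.
- g = 20%: 1.2³ − 1 = 0.728, or 73%, as Appendix 5 states.
- g = 30%: 1.3³ − 1 = 1.197, or 120%.

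The two limits are therefore not interchangeable.

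**2. Width of the conflicting band.** Let S be the reference sum of diameters. The upper limit is 30% (PMR row). The lower limit is 20% under Appendix 4 alone, or max(20%, 5 mm / S) with the Section 6.5 floor. Section 3.1 admits solitary tumours up to 6.5 cm and a total diameter up to 8 cm.

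| S (mm) | 5 mm / S | Band with floor | Growth in mm |
|---|---|---|---|
| 15 | 33.3% | empty | – |
| 16.7 | 30.0% | closes here | 5.0 |
| 20 | 25.0% | 25–30% | 5.0–6.0 |
| 25 | 20.0% | 20–30% | 5.0–7.5 |
| 45 | 11.1% | 20–30% | 9.0–13.5 |
| 65 | 7.7% | 20–30% | 13.0–19.5 |
| 80 | 6.3% | 20–30% | 16.0–24.0 |

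**3. Does another PERCIST rule close the band?** Take S = 45 mm at baseline and nadir, growth of 25% (11.25 mm), SUL peak down 30% with a fall of at least 0.8 units, and no new lesion.
- PMR number: 25% is not above 30%, so PMR is allowed.
- Appendix 4: 25% is at least 20%, and 11.25 mm exceeds 5 mm, so the scan shows RECIST progression.
- Metabolic progression by SUL: SUL fell, so it does not apply.
- Metabolic progression by extent: this needs a 75% TLG/TLA increase with no decline in SUL. SUL declined. If uptake volume scales with diameter cubed and mean SUL falls with the peak, TLG changes by 1.25³ × 0.7 − 1 = +37%. At 20% growth the change is 1.728 × 0.7 − 1 = +21%, and at 30% it is 2.197 × 0.7 − 1 = +54%. All are below 75%.

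No other rule closes the band.

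**4. Reference point.** RECIST counts from nadir, while the PMR row names no reference for size. If size is read from baseline, the overlap widens. With a nadir at 70% of baseline, RECIST progression occurs at 1.2 × 0.70 = 84% of baseline, where the PMR number sees no growth at all.

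**5. Weight of one patient.** 1/28 = 3.6 percentage points of the response rate.

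**The case against.** The strongest reply is that the parenthesis already settles the matter. It states what the condition means, so a patient with RECIST progression is not PMR and the 30% is a loose paraphrase. That is a fair reading, but the row does not say that the explanation overrides the number. The words that follow foresee PMR alongside anatomical progression. The ambiguity stands.

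A reader might go further and infer that such a patient is a responder and a progression event at once. The documents do not establish that:
- The row requires verification of anatomical progression. Without clinical deterioration, Section 6.5 requires a second scan, so one scan at +25% is not a confirmed progression.
- The Synopsis bases the event on "radiologically confirmed progressive disease based on RECIST 1.1, mRECIST, PERCIST or death from any cause", which can be read as any one criterion. Sections 2.1 and 8.1.1 join the three with a conjunction. Read strictly, a patient in PMR lacks PERCIST progression and has no event.

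A reader might also infer that one such patient decides the trial, because an exact two-sided binomial test against 60% gives p = 0.053 for 22/28 and 0.019 for 23/28. But Section 8 names neither the test nor the criterion to which 60% and 85% apply. The normal approximation for 22/28 gives z = (0.786 − 0.600) / √(0.6 × 0.4 / 28) = 2.01, p = 0.045. Any discrete test turns on one patient somewhere, so this does not measure the defect.

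Finally, some disagreement between metabolic and anatomical criteria is inherent in using three systems. That is true, and it is not the complaint. The complaint is that one row states a threshold and mislabels it.

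**Conclusion.** The point holds as an internal error in the definition of a co-primary response endpoint. The size limit in the PMR row does not match the RECIST progression it claims to express. The same patient can be classified either way for growth of 20–30%, narrowed by the 5 mm floor for sums below 25 mm and removed at about 16.7 mm or less.

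Inside that band the direction is one-sided: using the number instead of the explanation can only add responders. Outside it, for very small sums, the number can be the stricter rule, since growth above 30% may still be under 5 mm.

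The count affected is unknown and probably small. A case needs growth inside the band, a fall of at least 30% and 0.8 units in SUL peak, no new lesions, and no other scan that already gives a best response. The consequence for progression-free survival is conditional on confirmation and on how the criteria combine, and is not part of this conclusion. The sample size is not affected.

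**What to change.** In the PMR row of Appendix 5, keep the 30% limit for SUL only. Replace the size limit with a condition such as: *no PD by RECIST 1.1 as defined in Appendix 4 and Section 6.5*. Keep the existing follow-up verification clause. This also settles the reference point, because Appendix 4 counts from nadir.

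The cost is an edit to appendix wording, and the PERCIST response rate may be marginally lower. A further rule, that a metabolic response is cancelled once anatomical progression is confirmed, is a debatable convention that a statistical analysis plan may supply. It is not needed to repair this row.
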